### Outcomes

#### Effectiveness

The primary effectiveness outcome will be incontinence (presence; absence). Measures will be taken at 6 weeks, 3 months and, for those recruited during the first three months, 12 months post stroke. The primary analysis will be of the 6-week data as conservative interventions for continence typically last six weeks [11,15], and an effect is most likely to be seen at this time point.

Secondary effectiveness outcomes will be: quality of life, frequency and severity of incontinence, urinary symptoms, activities of daily living (ADLs), and death; at 6 weeks, 3 months and, for those recruited during the first three months, 12 months post stroke.

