#### Outcomes

The primary analysis set will be defined as the intention-to-treat population. All stroke services randomised will be retained in the trial. Outcome data will be collected from all consented patients whenever possible, whatever their level of subsequent engagement with the allocated intervention programme. If there is more than 10% loss to follow-up overall or moderately differential loss to follow-up across stroke services, a secondary per-protocol analysis will also be considered. The decision as to whether a per-protocol analysis will be informative will be made by the trial statistician in conjunction with other members of the Trial Management Group; this decision will be made without reference to the recorded values of the outcome data.

To account for the cluster randomisation, we shall use mixed effects modelling for continuous, ordinal and dichotomous outcomes to compare the two groups on primary and secondary outcome data. Baseline measures of the outcomes variables (where appropriate), stroke classification, type of incontinence and the other prognostic patient-level information (from the Edinburgh case-mix adjuster) will be included as individual-level covariates in the models for outcome data.

Missing outcome data will be imputed according to the particular outcome. For the primary analysis, dichotomous and ordinal outcomes for those who withdraw, die or are otherwise lost to follow-up will be imputed using a worst-case scenario (e.g. for the primary outcome variable, all those for whom incontinence status is not recorded at 6-weeks post-stroke will be assumed to be incontinent). For continuous outcomes, the primary analysis will use a non-parametric multiple imputation approach [66].

The effect of stroke service-level factors will also be explored in the modelling; this will enable appropriate stratification to be used in the future larger scale trial, if desired, and to potentially reduce the size of the intra-stroke service correlation coefficient by reducing the unexplained component of the variability between stroke services. This analysis will be used to confirm the sample size necessary for the future trial and to provide estimates (including 95% confidence intervals) of the effectiveness of each intervention relative to usual care.

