Various sensitivity analyses will be performed. These will assess: the robustness of assumptions inherent in the analyses (including the use of alternative analytical approaches given the small number of clusters and of alternative approaches to imputation of missing outcome data); the effect of excluding patients subsequently found **not **to have had a stroke from analyses and the impact on the estimate of effectiveness of including patients with pre-stroke incontinence.

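### Scoring death, withdrawal and non-response alike as incontinent in the primary analysis biases the arm comparison if loss is unequal, and shifts the pilot's planning figures even if it is equal

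*Protocol article*

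**What the plan says.** All of this is in the Protocol article. Under Data analysis, Outcomes, the primary rule for binary and ordinal outcomes is that "dichotomous and ordinal outcomes for those who withdraw, die or are otherwise lost to follow-up will be imputed using a worst-case scenario". For the primary outcome this means that "all those for whom incontinence status is not recorded at 6-weeks post-stroke will be assumed to be incontinent". Continuous outcomes are treated differently: "For continuous outcomes, the primary analysis will use a non-parametric multiple imputation approach".

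The same section gives the results a planning role: "This analysis will be used to confirm the sample size necessary for the future trial and to provide estimates" of each intervention's effectiveness against usual care, with 95% confidence intervals. That sentence follows the one on service-level factors. I read it as covering the mixed modelling of outcome data, to which the primary imputation rule applies. Sample Size adds that the pilot should help to confirm the ICC and the number of sites.

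Two provisions bear on missing data. One is a trigger: "If there is more than 10% loss to follow-up overall or moderately differential loss to follow-up across stroke services, a secondary per-protocol analysis" will be considered. The other is a set of sensitivity analyses that includes "alternative approaches to imputation of missing outcome data", without naming them.

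Under Outcomes, Effectiveness, the primary outcome is presence or absence of incontinence. Death is a separate secondary outcome, in the list that ends "activities of daily living (ADLs), and death".

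**The concern.** The outcome is defined as leakage reported on one questionnaire item. The rule turns it into leakage, death, withdrawal or no questionnaire. A between-arm contrast on that mixture reflects retention and survival as well as continence.

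Worst case sounds cautious, but it is cautious only about the rate within one arm. For a difference between arms it can hide a benefit or create one, depending on which arm loses more participants. The article itself foresees unequal loss across services, and with four services per arm a few services with poor retention can become an arm difference.

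The planning role is the second issue. Retention is a feasibility objective in its own right. If loss is already built into the incontinence rate and the effect, the planning figures mix two quantities that the full trial needs separately.

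**Working it through.** **Inputs from the article.** 780 participants in 12 services and 3 arms: 780/3 = 260 per arm, 780/12 = 65 per service. There is no power calculation, so there is no stated figure to reproduce and none is wrong because of this point.

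**Assumed inputs.** Six-week incontinence rate p from 0.25 to 0.60, loss l from 10% to 20%, and ICC from 0 to 0.05. The article gives none of these for six weeks. Background reports 40–60% incontinent in hospital and 25% at discharge. The crude ratios 25/60 = 0.42 and 25/40 = 0.63 suggest that the middle of the range is plausible, but they ignore deaths and discharge is not six weeks.

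**1. Analysed rate.** With true rate p, and missing participants like those observed, the analysed rate is l + (1 − l)p.

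**2. No true effect.** The difference between arms becomes (1 − p) × (difference in loss). At p = 0.50 with 10% and 20% loss: 0.10 + 0.90 × 0.50 = 55% against 0.20 + 0.80 × 0.50 = 60%, a spurious 5 points.

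| p | loss 10% vs 20% | loss 10% vs 15% | equal loss |
|---|---|---|---|
| 0.25 | 7.5 points | 3.75 | 0 |
| 0.40 | 6.0 | 3.0 | 0 |
| 0.50 | 5.0 | 2.5 | 0 |
| 0.60 | 4.0 | 2.0 | 0 |

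If missing participants truly have a higher rate r, replace (1 − p) by (1 − r). At r = 0.80 a 10-point gap gives 0.20 × 10 = 2 points.

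**3. True effect, 50% (usual care) vs 40% (programme).**
- Loss 10% vs 20%: 55% vs 52%, so 10 points become 3.
- Loss 20% vs 10%: 60% vs 46%, so 10 points become 14.
- Loss 20% in both: 60% vs 52%, so 10 × (1 − 0.20) = 8 points.

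**4. Planning under equal loss.** Two-sided 5%, 80% power, before any design effect:
- 50% vs 40% needs 388 per arm, or 388/0.80 = 485 allowing for 20% loss. The imputed 60% vs 52% needs 604. Inflating that again for loss gives 604/0.80 = 755, which counts attrition twice.
- 25% vs 15% needs 250, or 313 allowing for loss. The imputed 40% vs 32% needs 564.

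**5. ICC.** Two effects oppose each other.
- Retention that varies between services adds (1 − p)² × Var(l) / [P(1 − P)], where P is the analysed rate. With p = 0.50, mean loss 20% and P = 0.60: 0.25 × 0.01/0.24 = 0.010 at SD 10 points, and 0.25 × 0.0225/0.24 = 0.023 at SD 15 points.
- Uniform loss dilutes real variation. With p = 0.50, service SD 7 points and 15% loss, the ICC falls from 0.0049/0.25 = 0.020 to 0.85² × 0.0049/(0.575 × 0.425) = 0.014.

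**6. Size against the pilot's precision.** At P = 0.60 and 260 per arm, the standard error is √(2 × 0.24/260) = 4.3 points before clustering. The design effect 1 + 64 × ICC makes it 6.5 points at ICC 0.02 and 8.8 at ICC 0.05. With 10% vs 20% loss and p from 0.25 to 0.50, the chance of a nominal p < 0.05 is 43% to 21% at ICC 0, 22% to 12% at ICC 0.02 and 14% to 8% at ICC 0.05. These use a normal approximation without a small-cluster correction, so they are indicative only.

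**The case against.** The best defence is the design. This is an exploratory pilot that promises estimates with confidence intervals, and the 5-point artefact is below one standard error at ICC 0.02 or more. Follow-up is thorough: hand delivery for those still in hospital, reminders, telephone or proxy completion, home visits, face-to-face interviews for aphasia and blinded data collectors. Retention is reported as an objective, and alternative imputations are promised without any trigger. Participants enter incontinent or catheterised, so failure is a plausible guess for those lost. If the full trial kept the same failure-scored outcome, the imputed rates would be its correct planning inputs.

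Most of this stands, and it lowers the severity. It does not remove the point. The bias does not shrink with sample size, the sensitivity analyses do not replace the primary estimate, and no such composite outcome is declared.

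A reader might infer more than the article supports:
- **That the rule always produces a false effect.** It does so only if loss or mortality differs between arms.
- **That it inflates the ICC.** The direction is open.
- **That the binary and continuous rules contradict each other for deaths.** The article says that imputation follows the particular outcome, and the continuous rule does not mention death. Handling of quality-of-life, Barthel and QALY values after death may properly be left to the statistical analysis plan.
- **That a survivors-only primary analysis is the cure.** It would condition on a post-randomisation event and depart from the stated intention-to-treat set.

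**Conclusion.** The point holds for binary and ordinal outcomes. The primary rule pools death, withdrawal and non-response as incontinence, and it is not conservative between arms. The spurious difference is (1 − p) times the gap in loss: 4 to 7.5 points for an assumed 10-point gap, 2 to 3.75 for a 5-point gap, zero for equal loss, and less if those lost truly do worse than those observed. Equal loss still shrinks a true difference by (1 − loss), raises the apparent rate and can shift the ICC either way. This matters because the modelling is to confirm the full trial's sample size. The per-protocol analysis tied to loss addresses adherence, not missing outcomes.

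The mechanism is certain; its size in this trial is not, because the article gives none of the rates. I rate it a recommended change in an exploratory pilot, not a must-fix.

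**What to change.** Before outcome data reach the statistician, amend the primary analysis of binary and ordinal outcomes:

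1. Separate death from unknown status.
2. For living participants with missing status, use multiple imputation that respects clustering, with baseline covariates, arm and service in the model.
3. State how death enters. One option that keeps the intention-to-treat set is a declared alive-and-continent outcome with death as failure, with a survivors analysis alongside.
4. Keep worst-case imputation, and add differential (tipping-point) imputation, as named sensitivity analyses.
5. Take the planning rates and ICC from this analysis, and report retention and mortality separately so that attrition is counted once.
6. Answer loss above 10%, or differential loss, with the missing-data sensitivity analyses instead of a per-protocol analysis.

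The cost is wording and modest programming. The downside is that the primary estimate then relies on missing-at-random for living non-responders, which the analyses in item 4 test.

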#### Ascertainment of outcomes

Presence/absence of incontinence will be measured by the International Consultation on Incontinence Questionnaire (ICIQ-UI Short Form) [51]. Absence of incontinence will be defined as the response 'never' to Question 3, 'How often do you leak urine?'; presence of incontinence will be defined as any other response to Question 3 (ranging from 'about once a week or less often' to 'all the time'). The ICIQ-UI Short Form has received a grading of A^new ^- highly recommended from the International Consultation on Incontinence Symptoms and Quality of Life Committee indicating published reports of acceptable reliability, validity and responsiveness in at least one study [52]. To our knowledge, the ICIQ-UI Short Form has not been used in the post-stroke population. We have conducted preliminary validation of the tool with six stroke survivors from our Patient, Public and Carer Involvement Group using the approach recommended by the ICIQ developers ([name], personal communication); all thought the tool was appropriate for use post-stroke and few problems were identified.

Quality of life will be measured using the Incontinence Quality of Life Instrument (I-QOL) [53,54] and the EuroQol (EQ-5D) [55]. Frequency and severity of incontinence will be ascertained using the Incontinence Severity Index [56]. Urinary symptoms will be measured using the Leicester Urinary Symptom questionnaire [57] and activities of daily living via the Barthel Index [58].

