### Economic evaluation

In this pilot trial, we will develop data collection tools to record resource use which will be used in a future, definitive trial. Tools will include: proformas for staff to record training and time spent on the intervention; a structured staff-observation schedule to allow independent assessment of time spent on the intervention; proforma to record resources (e.g. tests and investigations, length of stay) used in hospital (data will be obtained from the hospital information system); postal questionnaire about health and social service input, for self-completion by patients and carers. The postal questionnaires will be based on a design used previously by the applicants when querying input after discharge in a cohort of stroke patients.

Two measures will be used for the cost-utility analysis. The EuroQol (EQ-5D)[55], a generic quality of life measure, will be used to facilitate comparison with other studies and will allow us to estimate the benefit of the intervention in terms of quality adjusted life years (QALYs) gained. However, it has been suggested that the EQ-5D has a large ceiling effect and poor responsiveness in a non-stroke sample of women with urinary incontinence [68]. We will therefore also use a condition-specific measure, the Incontinence-Specific Quality of Life instrument (I-QOL, [52,53]), which has been shown to be the best continence-specific measure for use in clinical trials in terms of reliability, validity and responsiveness to change [67].

We will build on the cost-utility analysis by conducting an additional sensitivity analysis. We will review published economic evaluations that have estimated Quality Adjusted Life Years (QALYs) and extract the utility (quality-of-life) values they used. We will tabulate the basis for these figures in terms of the size of sample, which patients were questioned, what technique was used (EQ-5D or other), and how values were derived. We will use the data which seem to have the most validity in the sensitivity analysis.

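### As naturally read, the plan multiply imputes continuous outcomes for participants who have died, so those comparisons become insensitive to mortality

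*Protocol article*

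**What the plan says.** Under Data analysis, Outcomes, the article first fixes the population: "The primary analysis set will be defined as the intention-to-treat population". It then sets the imputation rule: "Missing outcome data will be imputed according to the particular outcome". So the method depends on the type of outcome, not on why the value is absent.

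Two rules follow. The first is that "dichotomous and ordinal outcomes for those who withdraw, die or are otherwise lost to follow-up will be imputed using a worst-case scenario". The second is that "For continuous outcomes, the primary analysis will use a non-parametric multiple imputation approach". The second sentence neither names deaths nor excepts them.

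Elsewhere, Outcomes, Effectiveness lists death as a secondary outcome in its own right, at the same visits as the others: "urinary symptoms, activities of daily living (ADLs), and death; at 6 weeks, 3 months" and, for early recruits, 12 months. Ascertainment of outcomes names I-QOL and EQ-5D for quality of life and the Barthel Index for daily living, without saying which are analysed as continuous. Economic evaluation says that the EQ-5D "will allow us to estimate the benefit of the intervention in terms of quality adjusted life years (QALYs) gained". It does not say how a death is valued or whether imputed scores enter the calculation.

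**The concern.** Multiple imputation estimates a value that exists but was not observed. After death no I-QOL or Barthel score exists, and in a QALY calculation the utility is 0 by convention. Observed scores come only from people alive at the assessment, so any value imputed for a participant who died is a living person's score.

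The two rules in the paragraph then pull in opposite directions. The same death is the worst result on a dichotomous or ordinal outcome and resembles survival on a continuous one. If mortality differs between arms, the first kind of comparison moves against the arm with more deaths, while the second hardly moves.

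Deaths should be expected here. Participants have had an acute stroke, are incontinent or catheterised, may be drowsy, and have no upper age limit; some are followed for 12 months. The pilot is also meant to confirm outcome measures for a full-scale trial, so a poor rule could be carried forward.

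**Working it through.** **Step 1: the text.** The paragraph on missing data covers all missing outcome data and splits it by outcome type. The people whose data are missing are described once, as "for those who withdraw, die or are otherwise lost to follow-up". The continuous rule follows directly, in an intention-to-treat set. The natural reading is that the same people are meant in both sentences. This is an inference: the article does not state outright that deaths are imputed on continuous scales. Nothing in it points the other way. The word primary in the continuous rule refers to the main analysis of each outcome; the trial's primary outcome is dichotomous and falls under the first rule.

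**Step 2: inputs.** The plan gives no figure to reproduce on this point: no expected mortality, utility or standard deviation. The values below are assumptions. For scale only, 780 participants in three arms is 780 / 3 = 260 per arm if arms are equal, so 5 percentage points of mortality is 0.05 × 260 = 13 participants.

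- d = proportion dead by the assessment in an arm, assumed 5% to 20%
- m = mean utility in survivors, assumed 0.4 to 0.6 and equal in both arms compared

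**Step 3: arm means.** With deaths imputed at the survivor mean, the arm mean is m. With deaths at 0, it is (1 − d)m. The excess is d × m, from 0.05 × 0.4 = 0.02 to 0.20 × 0.6 = 0.12.

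**Step 4: difference between two arms.** With imputation at the survivor mean, it is m − m = 0 whatever the mortality. With deaths at 0, it is (1 − d₁)m − (1 − d₀)m = −(d₁ − d₀)m.

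| Mortality, two arms | Imputed | Deaths at 0, m = 0.4 | Deaths at 0, m = 0.6 |
|---|---|---|---|
| 10% v 10% | 0 | 0 | 0 |
| 10% v 15% | 0 | −0.02 | −0.03 |
| 10% v 20% | 0 | −0.04 | −0.06 |

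**Step 5: the same deaths on the primary outcome.** Assume half of survivors are incontinent in both arms. Under the worst-case rule, 10% v 15% mortality gives 0.10 + 0.90 × 0.5 = 0.55 and 0.15 + 0.85 × 0.5 = 0.575, a difference of 2.5 percentage points. The dichotomous comparison registers the deaths; the continuous one does not.

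**Step 6: if imputed values are lower than the survivor mean.** Prognostic covariates could give the dead a lower value k. The difference removed is then (d₁ − d₀)k. With k at half of m (0.2 to 0.3), a 5-point difference loses 0.05 × 0.2 = 0.01 to 0.05 × 0.3 = 0.015. The effect shrinks but does not vanish.

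**The case against.** The strongest reply is that the plan never says it imputes the dead on continuous scales. The phrase naming deaths sits in the dichotomous and ordinal sentence, the imputation method is given by a citation that is not at hand, and an analysis plan is to be finalised before outcome data reach the statistician. The instruments are not classified, and Barthel or the EQ-5D items could be analysed as ordinal, where death is already the worst case. Sensitivity analyses with other imputation methods are planned. The size is wholly assumed, and nothing suggests that a voiding programme alters mortality.

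Much of this limits the point without removing it. The article does more than leave detail to an analysis plan: it names death as a missing-data reason and fixes the method for continuous outcomes. An analysis plan that applied it literally would impute deaths. Some outcomes must be continuous, since models for them are planned, and a QALY needs a numeric utility. The planned sensitivity analyses still treat the values as missing and do not separate deaths.

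Three stronger readings are tempting and are not supported.

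- A reader might infer that a mortality harm would be hidden. It would not: death is a separate secondary outcome at each time point, and Trial management and monitoring provides a Data Monitoring Committee that meets twice a year.
- A reader might infer that QALYs are credited after death. Economic evaluation does not link QALYs to the imputed data; it is silent on deaths.
- A reader might infer that EQ-5D, I-QOL and Barthel are all affected. The article does not say which are continuous.

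**Conclusion.** The point holds as a defect in the stated rule for continuous outcomes. Death is treated as a reason for missing data and is not excepted from multiple imputation. On scales analysed as continuous, the comparison becomes insensitive to mortality and runs opposite to the worst-case rule in the same paragraph. This rests on the natural reading of three consecutive sentences, not on an explicit statement.

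The size is modest and illustrative: 0.02 to 0.03 in mean utility for a 5-point mortality difference, given survivor utility of 0.4 to 0.6, equal in both arms, and imputation near the survivor mean. With equal mortality there is no between-arm bias and only the arm means are too high. The primary outcome is not touched.

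**What to change.** Under Data analysis, Outcomes, restrict multiple imputation to participants known to be alive at the assessment, and report each continuous outcome as an estimate in survivors, beside deaths by arm at that time point. Under Economic evaluation, state that EQ-5D utility is 0 from the date of death in any QALY calculation. Naming the scales that are analysed as continuous would settle how far the rule reaches.

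The cost is wording in the protocol and analysis plan, plus a date of death for each participant who dies; death is already an outcome. There is one small downside. The continuous outcomes become survivor estimates, conditional on a post-randomisation event. They do not themselves penalise an arm with more deaths, so they must be read together with mortality. Only the QALY rule brings the deaths into the number itself.

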### Sample Size

The sample size is chosen pragmatically, rather than on the basis of a formal power calculation; our aim is to balance practicalities and the need for reasonable precision in the estimation of effects to inform the sample size calculation for a full-scale trial to test effectiveness.

The use of four stroke services per arm (12 in total) will provide a satisfactory indication of likely effectiveness and help us address any feasibility issues relating to the delivery of the interventions. It will also provide some degree of confirmation regarding the size of the intra-class correlation coefficient and will enable us to perform a review of the number of sites (and the number of patients needed per site) for each arm of the trial for a full-scale trial. It will also provide some information on stroke service-level factors which may help explain the variability in outcome between stroke services in each arm, thus helping reduce the intra-class correlation coefficient and hence achieve efficiency in terms of the number of stroke services required for a full-scale trial.

Twelve stroke services will admit around 4800 patients per year, of whom we expect around 20% will meet the trial inclusion criteria and consent to participate. To achieve better balance in the number of participants recruited per Trust, we will recruit for 12 months in services which admit 300 or less patients per year and for 9 months in Trusts which admit more than 300 patients per year; we expect that this will enable us to recruit 780 patients across the 12 services.

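### The full trial's size is to be confirmed from a model that explores service-level factors on 12 services: the ICC may be biased low if factors are kept by fit, and is too imprecise as a single value in any case

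*Protocol article*

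**What the plan says.** The Aim section makes estimating how many sites and patients a full-scale trial needs one of the pilot's purposes. Two later sections say how the service-level correlation serves it.

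- **Sample Size.** On the ICC: "It will also provide some degree of confirmation regarding the size of the intra-class correlation coefficient". The same paragraph expects service-level factors to help explain variation between services, so lowering the ICC and cutting the number of services a full trial needs.
- **Data analysis, Outcomes.** Service-level factors are to be explored in the outcome models. One reason is to permit stratification in the later trial, if that is wanted. The other is "to potentially reduce the size of the intra-stroke service correlation coefficient by reducing the unexplained component of the variability between stroke services". The next sentence reads "This analysis will be used to confirm the sample size necessary for the future trial".

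The article gives no ICC value, no list of service factors for these models, and no statement of which ICC (with or without service factors, point value or limit) will set the later sample size. It promises 95% confidence intervals for the effect estimates and mentions none for the ICC. The service-level factors it names in connection with allocation are the three behind the randomisation strata (Sequence generation): unit structure, audit performance and annual admissions.

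**The concern.** Exploration, a lower ICC and a smaller full trial are joined in the article's own text, in two sections. Twelve services in three arms leave little information between services. If several service characteristics are tried and those that seem to explain outcome variation are retained, chance alone makes worthless factors look useful, and the residual between-service variance is understated. That residual ICC enters the design effect directly, so the definitive trial would be planned with too few services.

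There is a second problem, independent of selection. With so few services the ICC is estimated very loosely, and one value taken from it cannot bear the weight of confirming a sample size.

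**Working it through.** **Inputs from the article.** 12 services, 4 per arm (Sample Size). Around 4800 admissions a year, with about 20% eligible and consenting; recruitment for 12 months in services with 300 or fewer admissions and 9 months elsewhere; target 780. No power calculation is offered: "The sample size is chosen pragmatically, rather than on the basis of a formal power calculation".

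**The article's own figure.** 4800 × 0.20 = 960 a year. Nine months everywhere gives 960 × 9/12 = 720; twelve months everywhere gives 960. To reach 780, a share s of admissions in 12-month services must satisfy 720 + 240s = 780, so s = 0.25 (for example 4 services at 300 each). The split is not given, but 780 is attainable. Mean cluster size is 780/12 = 65.

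**Assumptions.** The article gives no ICC, so a true value of 0.05 is assumed (0.02 and 0.10 were also run, with the same pattern). Outcomes are treated through normally distributed service means, a continuous approximation to the binary primary outcome. Candidate factors are pure noise.

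**Step 1: precision with no service factors.**
- Between-service df = 12 − 3 = 9; within-service df = 12 × 64 = 768.
- For an observed ICC of 0.05, F = (1 + 64 × 0.05)/(1 − 0.05) = 4.2/0.95 = 4.42.
- The 2.5% and 97.5% points of F(9, 768) are 0.299 and 2.130, so the limits for the variance ratio are 4.42/2.130 = 2.08 and 4.42/0.299 = 14.78.
- With ICC = (F − 1)/(F + 64), the 95% CI is 0.016 to 0.175.
- Design effect 1 + 64 × ICC: 2.0 to 12.2, against 4.2 at the point value.
- Upper one-sided 80% limit: 4.42/0.597 = 7.40, giving ICC 0.090. If the four strata are also fitted, 3 more df go; on 6 df the limit is 4.42/0.511 = 8.65, giving ICC 0.105.

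**Step 2: effect of choosing factors by fit.** Simulated pilots (at least 4000 per setting), true ICC 0.05, df-corrected between-service variance. Power is for a full trial planned at 80% using the mean estimated ICC when the truth is 0.05: Φ(2.80 × √(DE planned/4.2) − 1.96).

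| Service factors in the model | Mean ICC | Design effect | Actual power |
|---|---|---|---|
| None | 0.049 | 4.1 | 79% |
| Three noise factors, pre-specified | 0.049 | 4.1 | 79% |
| Best 1 of 3 noise factors | 0.042 | 3.7 | 74-75% |
| Best 2 of 5 noise factors | 0.033 | 3.1 | 67-68% |

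Worked row, best 1 of 3: DE = 1 + 64 × 0.042 = 3.69; √(3.69/4.2) = 0.937; 2.80 × 0.937 − 1.96 = 0.66; Φ(0.66) = 0.75.

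**Step 3: separating selection from imprecision.** A second calculation averages realised power over the whole distribution of ICC estimates, for a full trial planned at 90% (assumed 60% v 50%, two-sided 5%, 65 per service). No service factors: 84%. Best 1 of 3: 79%. So in the mildest case selection costs about 5 points, and about 6 points of the shortfall from 90% come from imprecision alone.

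**Step 4: when adjustment is sound.** A genuine pre-specified factor explaining 40% of between-service variance has a true residual ICC of 0.031; the mean estimate is 0.030. By contrast, three pre-specified noise factors with uncorrected maximum-likelihood variance give a mean of 0.019, so the df correction matters as well as the pre-specification.

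**The case against.** A reader might infer that the plan will search service factors by fit and will therefore produce an ICC that is too low and an underpowered definitive trial. The article does not support that. It says the factors will be explored; it gives no selection rule, and does not say that only the adjusted point estimate will be used. Factor lists, estimation method and the ICC limit for sizing may sit in an analysis plan that is not shown, and the Blinding section says that plan is finalised before the statistician has outcome data. The wording is also guarded: the Sample Size section claims only partial confirmation of the ICC, and sensitivity analyses are planned in view of the small number of clusters.

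Reducing the ICC with service-level covariates is a proper aim when the factors are real and the full trial stratifies on or adjusts for them. The sentence containing the quoted text mentions such stratification.

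All of that stands, and it makes the bias conditional. What remains is that the article itself sends the exploratory model's output to the sample size. Stratification in the full trial is left optional, so the lower ICC is not tied to a design that would earn it. The small-cluster sensitivity analyses set no rule on which ICC is used. The imprecision in Step 1 needs no assumption about selection.

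**Conclusion.** The point holds in conditional form. As written, the article links exploratory service-factor modelling on 12 services to a lower ICC and to confirming the full trial's size.

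- If factors are kept because they seem to explain variance, the residual ICC risks being biased low: from 0.05 to about 0.042 for the best 1 of 3 (the number of stratification factors the article names) and about 0.033 for the best 2 of 5, with actual power of about 74-75% and 67-68% against 80% planned.
- With pre-specified factors and df-corrected variance there is no mean bias.
- Whatever is done about factors, an observed ICC of 0.05 is compatible with about 0.016 to 0.175, a sixfold range in design effect (12.2/2.0). A point value cannot confirm a sample size.

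The true ICC, equal cluster sizes of 65, the number of candidate factors and the continuous approximation are assumptions. Worth correcting, because sizing the full trial is a stated aim of the pilot.

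**What to change.** In Data analysis, Outcomes, change the rule for the future sample size:

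1. Base it on the ICC from the pre-specified model with arm and patient covariates and no explored service factors, reported with its confidence interval.
2. Show the required number of services across that interval, including a conservative value such as the upper one-sided 80% limit. For an estimate of 0.05 this is about 0.09 on 9 df, or about 0.105 on 6 df if the strata are also fitted.
3. Label models with explored service factors as hypothesis-generating.
4. Use a service-adjusted ICC for sizing only for pre-named factors, with df-corrected (REML-type) variance, that the full trial will itself stratify on or adjust for.

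The cost is wording only; no further data are needed. The downside is that the projected full trial becomes larger: at an ICC of 0.09 the design effect is 1 + 64 × 0.09 = 6.8 against 4.2 at 0.05, about 60% more patients and services at the same cluster size.
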